### 2.3. Randomization

Participants will be assigned to study arms after completion of the baseline enrollment survey. The study staff who enrolls each participant will notify the study biostatistician, who will provide the allocation. Randomization will be conducted using a computer-generated, permuted block randomization sequence stratified by dyad type (with or without mild AD/ADRD). Within each stratum, randomization will be performed using permuted blocks of 4 to ensure balanced group sizes. Both members of the dyad will be randomized together to the same intervention or control arm. The randomization sequence will be generated in advance by the study biostatistician using a random number generator and securely maintained within the study database, accessible only after baseline data collection is completed. After the third week of intervention, we will have a one-week crossover period, and all participants will switch to the alternate study arm. This one-week crossover period is a washout period to minimize the effects of promptings and motivations produced by the text messages, rather than to eliminate retained knowledge or behavior change. Group assignments will remain linked to each participant’s unique study ID throughout the study. The analyst will remain blinded to group assignments until data cleaning, feasibility, and preliminary efficacy analyses are complete.

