Preliminary Efficacy Assessment: Using linear mixed-effects models, we will estimate the effect size of the ACTIVE intervention’s preliminary efficacy on the three activity metrics and seven post-intervention behavioral measures (listed above). The effect size will be estimated from the pre-crossover phase (Equation (5)). Full six-week mixed-effects models are used to evaluate whether longitudinal patterns remain consistent with the pre-crossover estimate, after accounting for the impact of the crossover and the sequence of intervention (Equation (6)). The random intercept will account for both within-dyad correlation and repeated measures. Fixed effects will include treatment (intervention vs. control), sequence (intervention first or last), baseline values of the outcomes, dementia status (mild AD/ADRD vs. no AD/ADRD), treatment × dementia interaction, period (pre-crossover vs. post-crossover), treatment × period interaction, and covariates to assess potential differential effects. For participant *i* in dyad *d* at time *t* (t = baseline, follow-ups), the outcome will follow the mixed effect model in Equations (1) and (2), as follows:(5)$${\;Y}_{idt}=\;\beta_{0}+\;\beta_{1}{Trt}_{i}+\;\beta_{3}{Time}_{t}+\;\beta_{5}Y_{id0}+\;\beta_{6}{Dem}_{i}+\;\beta_{7}\left({Trt}_{i}\;\times \;{Dem}_{i}\right)+\;\tau^{T}X_{i}+\;b_{d}+\;b_{i\left(d\right)}+\;\in_{idt}\;\;$$(6)$$Y_{idt}=\beta_{0}+\beta_{1}{Trt}_{i}+\beta_{2}{Seq}_{i}+\beta_{3}{Time}_{t}+\beta_{4}{Period}_{t}+\beta_{5}Y_{id0}+\beta_{6}{Dem}_{i}+\beta_{7}\left({Trt}_{i}\times {Dem}_{i}\right)+\beta_{8}\left({Trt}_{i}\times {Period}_{i}\right)+\tau^{T}X_{i}+b_{d}+b_{i(d)}+\in_{id\;\;\;\;\;\;\;\;}$$

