where *Y_idt_* = outcome, *β*_0_ = fixed intercept, *Trt_i_* = treatment indicator, *Seq_i_* = sequence indicator, *Y_id_*_0_ = baseline value of the outcome, *Demi* = dementia status, *Trt × Dem* = treatment-by-dementia interaction, *Trt × Period =* treatment-by-crossover interaction, γ^⊤^*X_i_* = coefficient of covariates, and *b_d_* and *b_i(d)_* are the random intercept for dyad and individual nested within dyad, respectively. Treatment condition (intervention vs. control) and sequence (intervention-first vs. intervention-second) will be included as fixed effects to estimate the average intervention effect and to account for between-participant differences related to assignment order, respectively. Time will be modeled as a continuous weekly measure to capture trends over the six-week follow-up. Period will be modeled separately as a categorical indicator of pre- versus post-crossover phase to distinguish underlying activity trajectories from changes associated with withdrawal of active intervention components. Given the anticipated persistence of learning effects due to the short one-week washout period, the treatment × period interaction will be used to characterize maintenance or attenuation of intervention effects rather than to assume their absence. All analytical models will follow the intention-to-treat principle, and effect sizes with 95% confidence intervals will be reported to inform power calculations for a future definitive trial.

Qualitative Assessment: Semi-structured interviews will be conducted with dyads after completing the intervention phases. Dyads initially randomized to the intervention arm will be interviewed at crossover, while those starting in the control arm will be interviewed after completing the delayed intervention. Interviews will explore barriers and facilitators to smartwatch use, motivational texts, instructional educational modules, engaging in video-guided physical rehabilitation, walking exercise, and co-participating with a care partner. While we estimate conducting 10 to 20 interviews each for those with and without mild AD/ADRD, the exact number will be guided by the achievement of thematic saturation [68,69].

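### Equation 6, the secondary six-week model, is rank deficient: sequence cannot be fitted alongside treatment, period and treatment × period in a two-sequence, two-period crossover

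*Protocol article*

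**What the plan says.** Section 2.3 sets up a crossover in which, after the third intervention week and a one-week washout, "all participants will switch to the alternate study arm". There are therefore two sequences and two periods. Section 2.7 places the analysed activity data in weeks 2–4 and 6–8. Data from weeks 1 and 5 are not used.

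Section 2.13 takes the effect size from the pre-crossover phase (Equation 5). It then uses Equation 6, over all six weeks, to see whether the longitudinal pattern agrees with that estimate. The model text reads "Fixed effects will include treatment (intervention vs. control), sequence (intervention first or last), baseline values of the outcomes" and continues, after dementia status and its interaction with treatment, with "period (pre-crossover vs. post-crossover), treatment × period interaction, and covariates to assess potential differential effects". Equation 6 accordingly carries Trt (β1), Seq (β2), Time (β3), Period (β4), the baseline value (β5), Dem (β6), Trt × Dem (β7), Trt × Period (β8), covariates, and random intercepts for dyad and person.

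The explanatory text gives the terms separate jobs:
- Sequence is there "to account for between-participant differences related to assignment order, respectively".
- On retained effects, "the treatment × period interaction will be used to characterize maintenance or attenuation of intervention effects rather than to assume their absence".
- "Period will be modeled separately as a categorical indicator of pre- versus post-crossover phase", with the stated aim of separating underlying trends from changes due to components being taken away.
- "Time will be modeled as a continuous weekly measure to capture trends over the six-week follow-up".

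**The concern.** A two-sequence, two-period crossover has four cell means. An intercept, treatment, period and treatment × period already describe all four, so sequence has nothing left to estimate. The plan nevertheless assigns assignment order to β2 and maintenance or attenuation to β8, as if the data could tell them apart.

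Software meeting such a model will drop a column, with or without a warning, or return one of many equivalent solutions. The reported sequence, period, interaction and treatment coefficients then depend on column order or coding. A chance difference between the two sequence groups could be reported as attenuation of the intervention effect, or attenuation as a sequence difference.

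The description of Period has a related problem. At the switch, one sequence has the intervention components removed and the other has them introduced. One coefficient shared by both sequences cannot stand for removal.

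**Working it through.** The plan gives no figure on this point, so the check is of the model as printed. It covers the activity outcomes, which have weekly rows in both arms.

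**Inputs.** Two sequences and a single switch (Section 2.3); six analysed weeks, three per period (Section 2.7); the Equation 6 terms and the coding of Period and Time (Section 2.13).

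**Step 1: the four cells, treatment time-varying, 0/1 coding** (Seq = 1 for intervention first, Period = 1 after crossover).

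| Sequence, period | Trt | Period | Trt × Period | Trt + Period − 2(Trt × Period) | Seq |
|---|---|---|---|---|---|
| Control first, pre | 0 | 0 | 0 | 0 + 0 − 0 = 0 | 0 |
| Control first, post | 1 | 1 | 1 | 1 + 1 − 2 = 0 | 0 |
| Intervention first, pre | 1 | 0 | 0 | 1 + 0 − 0 = 1 | 1 |
| Intervention first, post | 0 | 1 | 0 | 0 + 1 − 0 = 1 | 1 |

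The last two columns agree in every cell. The five columns (intercept, Trt, Seq, Period, Trt × Period) have rank 4. With ±1 coding, Seq equals Trt × Period up to sign, so the conclusion does not depend on coding.

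**Step 2: do the other terms help?** I enumerated 2 sequences × 6 weeks × 2 dementia levels, with eight columns: intercept, Trt, Seq, Time, Period, Dem, Trt × Dem, Trt × Period.

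| Reading of treatment | Full model | Drop Seq | Drop Trt × Period |
|---|---|---|---|
| Time-varying | rank 7 of 8 | 7 of 7 | 7 of 7 |
| Fixed at assigned arm, as the subscript is printed | rank 7 of 8 | 7 of 7 | 6 of 7 |

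Adding the baseline value and two example covariates for 50 dyads of two gives 11 columns and rank 10 under either reading. Time is common to both sequences and does not break the dependency. Random intercepts do not cure a deficiency in the fixed effects.

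Under the fixed reading the aliased pair is different. Trt equals Seq, so β1 and β2 are confounded and β8 is estimable. Dropping the interaction then repairs nothing.

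**Step 3: what the coefficients would say.** Take illustrative noiseless values, not trial data, with treatment time-varying: intercept 5, treatment effect 2, sequence difference 1, no period effect and no interaction. The cell means are:
- control first: 5, then 5 + 2 = 7;
- intervention first: 5 + 2 + 1 = 8, then 5 + 1 = 6.

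Two reduced models fit these means exactly:
- Trt × Period dropped: Trt = 2, Seq = 1, Period = 0.
- Seq dropped: Trt = 3, Period = 1, Trt × Period = −2.

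The second shows an apparent attenuation of 2 where none was put in.

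Carryover gives the same means. Take a treatment effect of 3, a period effect of −1 and a carryover of 2 into the control period. Control first is then 5, and 5 − 1 + 3 = 7; intervention first is 5 + 3 = 8, and 5 − 1 + 2 = 6.

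**Step 4: what survives.** The intervention-minus-control difference is 8 − 5 = 3 before crossover and 7 − 6 = 1 after. Both reduced models return these values: 2 + 1 = 3 and 2 − 1 = 1 with Seq kept; 3 and 3 − 2 = 1 with the interaction kept. Cell means and period-specific differences do not depend on which column goes.

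**The case against.** **Baseline rows.** Section 2.13 lists baseline among the time points of the outcome. If baseline rows enter and are coded untreated in both sequences, the rank rises to 8 of 8. This does not rescue the plan. The baseline value is already a covariate in the same equation, the follow-up is described as six weeks, and week 1 activity data are discarded. If baseline rows are coded by assigned arm, the rank stays at 7 of 8. Even where rank is restored, sequence would be identified only from baseline imbalance.

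**Carryover is acknowledged.** Section 2.3 says the washout is not meant to erase retained knowledge or behaviour, and Section 2.13 expects learning effects to persist. Under randomisation the sequence difference is zero in expectation. With Seq dropped, the interaction then reflects carryover together with treatment-by-period change, plus chance imbalance. That is close to what the authors want, so it would be too strong to say β8 has nothing to do with maintenance. What stands is that it cannot separate maintenance from a treatment effect that differs by period, or from a chance sequence difference.

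**Stronger readings a reader might infer.** One is that the trial's effect estimate is invalid. The documents do not support this: the effect size comes from Equation 5, which contains none of Seq, Period or Trt × Period, and the go/no-go decision rests on feasibility benchmarks. Another is that the whole comparison of six-week patterns with the pre-crossover estimate is meaningless. Step 4 of the working shows otherwise: individual coefficients lose their meaning, while the period-specific differences needed for that comparison remain estimable.

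**Leaving it to a later analysis plan.** A fuller document could settle details, but the article prints the equation and assigns the interpretations, so this is something stated wrongly, not something left out.

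**Conclusion.** The point holds for Equation 6. With treatment time-varying and only the six analysed weeks as outcome rows, β2 and β8 cannot both be estimated, and β1 depends on which column is removed. In the illustration it is 2 or 3 for identical data. With treatment fixed as printed, β1 and β2 are aliased instead. Under either reading one of the eight main fixed-effect columns is redundant.

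The separate roles given to sequence and to treatment × period cannot be delivered by this design, and Period cannot stand for withdrawal of components.

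The conclusion rests on two sequences, one switch, a two-level Period and no separately coded baseline outcome rows, as the current text describes. Because the damage is limited to coefficients of a secondary model in a pilot not powered for efficacy, this should be fixed before analysis but is not a critical defect.

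**What to change.** 1. Write treatment with a time index (Trt_it) in Equation 6. This must come first, because removing the interaction does not restore rank while treatment is fixed at the assigned arm.
2. Keep only one of Seq_i and Trt_it × Period_t, and say which.
3. If the interaction is kept, state that it cannot separate carryover or maintenance from treatment-by-period change or from a chance sequence difference.
4. Base the comparison with Equation 5 on the intervention-minus-control difference in each period, reported with confidence intervals.
5. Remove the statement that Period captures the withdrawal of active components.

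The cost is one equation and one paragraph of text. Data collection, randomisation and Equation 5 do not change.

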### 2.7. Study Procedure

The study will run for 10 weeks (Figure 2), starting with a one-week pre-intervention phase, followed by three weeks of intervention (or control), one week crossover phase, three weeks of control (or intervention), and a two-week post-intervention phase. The 3-week intervention period was selected to balance feasibility assessment with participant burden, consistent with pilot study methodology [39,40]. This duration provides adequate time to evaluate key feasibility outcomes while generating preliminary effect estimates to inform sample-size calculations for a definitive trial. Prior digital health intervention pilots have used a similar intervention period to assess the feasibility of technology-based interventions [41,42,43].

Week 1 (Pre-Intervention): The study team will call the dyad to confirm receipt of the study materials and ensure: (1) the appropriate wearing of the Fitbit smartwatches and data capture, (2) receipt of motivational text messages, and (3) access to the educational videos (Table 2). Data collected during this week will not be used for the study.

Weeks 2–4 (Phase I Intervention/Control): The intervention will start with dyads randomized to the intervention arms. Remote tracking of physical activity data will continue in the control arm.

Week 5 (Crossover/Washout): Participants will switch arms (intervention to control and vice versa). Activity data during this crossover week will not be analyzed (Table 2). Participants in the intervention arm will complete six post-intervention surveys (discussed below), and a few will participate in interviews.

Weeks 6–8 (Phase II Intervention/Control): Participants will continue in their new assignments (opposite of initial condition).

Weeks 9–10 (Post-Intervention): Crossover participants in the intervention arm will undergo post-intervention surveys and interviews. All participants will have access to the educational videos and video-guided physical rehabilitation sessions upon completion of the study (Table 2).

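### Read literally, Equation 5 makes baseline both a response and a covariate, which shrinks the treatment coefficient; under 0/1 dementia coding that coefficient is also one stratum's effect, not the average

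*Protocol article*

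**What the plan says.** All of this is in section 2.13 (Analysis Plan) of the protocol article unless noted.

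- Source of the effect size: "The effect size will be estimated from the pre-crossover phase (Equation (5".
- Response occasions: "t = baseline, follow-ups), the outcome will follow the mixed effect model".
- Right-hand side, among other terms: "baseline values of the outcomes, dementia status (mild AD/ADRD vs. no AD/ADRD), treatment × dementia interaction". In Equation 5 these are β5·Y_id0, β6·Dem and β7·(Trt×Dem).
- Treatment: "Trt_i_* = treatment indicator", with subscript i only. Equation 5 has a Time term but no Trt×Time term.
- Purpose of the treatment and sequence terms: they "will be included as fixed effects to estimate the average intervention effect" and to account for assignment order.
- Time: "Time will be modeled as a continuous weekly measure to capture trends over the six-week follow-up".
- Use of the result: "effect sizes with 95% confidence intervals will be reported to inform power calculations for a future definitive trial".

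The pre-crossover phase follows the pre-intervention week, which is "followed by three weeks of intervention (or control" in section 2.7.

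**The concern.** A baseline value can be a response or a covariate. When it is both, the baseline row is predicted by itself and cannot show a treatment difference. If the treatment variable already carries the assigned arm on that row, and no term lets the effect start later, one coefficient has to fit a zero at baseline and the real effect afterwards. It settles in between.

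The second issue is which effect β1 stands for. Once Trt×Dem is in the model, β1 is the treatment effect where Dem equals zero. Under ordinary 0/1 coding that is the dyads without AD/ADRD, 25 of the 50 planned (section 2.2). The text nevertheless describes the treatment term as giving the average effect.

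At stake is a planning input. The protocol gives effect sizes with confidence intervals as the product of these models and names the definitive trial's power calculation as their use.

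**Working it through.** The protocol states no figure for Equation 5. Its only precision figures, in section 2.8, do reproduce: √(0.75×0.25/100) = 0.0433, times √1.2 = 0.0474, giving 0.657 to 0.843. They concern a feasibility proportion and do not bear on this point.

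**Step 1: dilution by algebra.** Let δ be the true effect on each of K follow-up rows, and let Trt be constant within a person.
- Follow-up row: E(Y | Y0, Trt) = a + r·Y0 + δ·Trt.
- Baseline row: Y = Y0, with no Trt term.
- In balanced data, β1 is a contrast of person means over all K+1 rows. The person mean is [Y0 + K(a + r·Y0 + δ·Trt)]/(K+1), so the coefficient of Trt is δ·K/(K+1).

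This factor does not depend on the variance components. For K = 3 it is 3/4.

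**Step 2: dilution by simulation.** Design inputs from the protocol are 50 dyads, 25 per stratum, two members each, balanced arms and three weekly follow-ups. Assumed inputs are variances of 0.2 (dyad), 0.4 (person) and 0.4 (residual), and a true effect of 0.50 in both strata. The model is Equation 5 without the covariates X, over 60 replicates.

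| Rows and coding | mean β1 | model SE | β1/SE |
|---|---|---|---|
| Follow-up rows only | 0.472 | 0.179 | 2.64 |
| Baseline row added, Trt = arm | 0.354 | 0.134 | 2.64 |
| Baseline row added, Trt = 0 at baseline | 0.487 | 0.120 | 4.06 |

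The ratio of the first two estimates is 0.354/0.472 = 0.75, and of their SEs 0.134/0.179 = 0.75. The estimate and its SE shrink together. The third row shows that the dilution disappears if Trt is zero before treatment starts.

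**Step 3: which effect β1 is.** Use the same design with assumed true effects of 0.8 (no dementia) and 0.2 (dementia), average 0.5.
- Follow-up rows only, Dem 0/1: β1 = 0.772, the no-dementia effect.
- Follow-up rows only, Dem −0.5/+0.5: β1 = 0.486 (Monte Carlo SE 0.017), the average.
- Equation 5 read literally, Dem 0/1: β1 = 0.579, which is 0.772 × 0.75. With the strata reversed it is 0.129.

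Precision: the SE is 0.179 for the single-stratum coefficient against 0.127 for the average, a ratio of 1.41. A separate check on dyad means gave 0.176 against 0.130, a ratio of 1.35.

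**Step 4: Equation 6.** Code Seq = 1 for intervention first and Period = 1 after crossover. On the post-baseline rows, Trt = Seq − Period + 2·(Trt×Period).

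| Seq | Period | Trt | Trt×Period | Seq − Period + 2·(Trt×Period) |
|---|---|---|---|---|
| 1 | 0 | 1 | 0 | 1 |
| 1 | 1 | 0 | 0 | 0 |
| 0 | 0 | 0 | 0 | 0 |
| 0 | 1 | 1 | 1 | 1 |

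The identity holds in every cell, so these four terms cannot all be estimated. Dropping the baseline row does not cure that.

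**The case against.** The strongest reply is that the problem is loose notation.

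- **Treatment coding.** Trt_i must change within a person in Equation 6, or it would duplicate Seq_i, so the missing time index proves little. If Trt is zero at baseline, there is no material dilution. This stands as a limit: the dilution belongs to the literal reading. But nothing says so for Equation 5.
- **Follow-up rows only.** The six-week wording for Time suggests that baseline is not a response row. It is a hint, and it conflicts with the explicit index. The two statements need reconciling.
- **Dementia coding.** No coding of Dem is given, and the average can be recovered from the same fit as β1 + 0.5·β7. True, but the plan attaches the average to the treatment term and defines no such combination. With equal effects in the two strata there is no bias, only a loss of precision.
- **Stakes.** Section 2.8 says the pilot is not powered for efficacy, and the go/stop rule uses feasibility benchmarks. This stands and lowers the severity.

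A reader might also infer specific damage to the next trial. Required sample size varies as 1/δ², so a factor of 3/4 suggests (4/3)² = 1.8 times too many participants, and a factor of 1/2 suggests 4 times. The documents do not support either as a figure for this trial. The 3/4 case needs an activity baseline, yet section 2.7 discards week 1 data and names no other source. The 1/2 case needs one pre-crossover survey in both arms, yet section 2.12 gives that survey to the intervention arm only. Under that schedule, simulation with the baseline row gives β1 = 0.000, with Time absorbing the effect.

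**Conclusion.** The point holds for Equation 5 as printed. In balanced data, with Trt equal to the assigned arm on the baseline row, β1 is K/(K+1) of the true effect: 3/4 for three weekly values, if an activity baseline exists. The harm is to the reported effect size and its interval, not to the test statistic. Under 0/1 coding of Dem, β1 is also the effect in dyads without AD/ADRD, with an SE about 35–40% larger than that of the average. The size of the gap between that effect and the average depends on how far the strata differ, which is unknown; the 0.8 and 0.2 above are illustrations.

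It would go too far to say that the trial's efficacy estimate will certainly be biased, because the codings behind both results are unstated. The missing control-arm survey before crossover is a separate defect that correcting Equation 5 does not cure. Severity: should fix.

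**What to change.** 1. In Equation 5, define t as the post-baseline, pre-crossover occasions only, with Y_id0 solely as a covariate. Alternatively, keep baseline as a response, drop Y_id0 and constrain the arms to be equal at baseline.
2. State the reported effect as the average over the two dementia strata. Any one of these will do: code Dem −0.5/+0.5; report β1 + 0.5·β7 under 0/1 coding; or take the effect from a model without Trt×Dem. Report Trt×Dem as exploratory.
3. State how Trt is coded on every row that enters each equation, and where the activity baseline comes from.
4. In Equation 6, remove one of Seq, Period, Trt or Trt×Period, and say what the remaining coefficients mean.

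With follow-up rows only and centred Dem, the simulation returned 0.486 (Monte Carlo SE 0.017) for a true 0.50, both with equal effects and with 0.8/0.2. Items 1, 2 and 4 cost only analysis-plan wording, with no new data and no change to the design. Item 3 is also wording, unless no activity baseline is being collected.
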